### Conceptual Framework

The study is based on aesthetic theory and social support theory. Aesthetic theory underscores the significance of aesthetic experience in enhancing well-being via emotional and sensory reactions to art [32,33]. Interaction with beauty is correlated with favorable emotional states, which neuroscience links to the release of neurotransmitters such as endorphins and serotonin as well as a decrease in stress-related indicators, including cortisol [34-37]. Social support theory emphasizes that interpersonal interactions mitigate stress and improve well-being by providing emotional, informational, and companionship support [38-42]. Aesthetic theory corresponds to the creative process of Chinese painting and calligraphy in the Chinese art activity component of this intervention, mainly supporting the mechanisms of changes in emotional states and self-esteem levels. Social support theory corresponds to the peer group participation component, mainly guiding the mechanism of changes in perceived social support and loneliness. The concept structure of this study is shown in Figure 1.

This study is an exploratory trial. PWB, happiness, relaxation, loneliness, and salivary cortisol levels were selected as the dependent variables. Happiness, relaxation, and loneliness are all operationally defined as an immediate, subjective, and transient affective state characterized by momentary feelings [43,44]. Usually, PWB requires intervention for a longer period to manifest changes. However, as an exploratory trial, we still included it as an exploratory outcome measure to provide preliminary data for future research.

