### Trial Design

This multicenter randomized, assessor-blinded trial is structured according to the “max-min-con” principle [45,46]: maximizing experimental variance by ensuring that art activities and art activities with peer group participation are delivered consistently and distinctly from the control condition; minimizing error variance by using standardized protocols for art activities and art activities with peer group participation, trained research assistants (RAs), and reliable measurement instruments; and controlling extraneous variance through minimized randomization and blinding of outcome assessors.

This study has 3 intervention groups: group A (Chinese art activities), group B (Chinese art activities+peer group participation), and group C (regular care), with participants randomized at a 1:1:1 allocation ratio. The study will be conducted consecutively at 3 older adult centers. These 3 centers all belong to Suzhou Health and Elderly Care Industry Development Group Co, Ltd. After on-site inspection, it was determined that the inclusion criteria (affiliation, bed capacity, facilities, management support, and accessibility) were met to ensure feasibility and reasonable representativeness. Each center is treated as a randomization unit. Figure 2 delineates the implementation phase and the data collection procedures in the study. The intervention takes place over 3 sessions in a single week (Monday, Wednesday, and Friday). Baseline evaluations of PWB, loneliness, happiness, relaxation, and salivary cortisol levels are conducted before randomization.

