**Figure 2. F2:**
[figure not shown]
The implementation phase and data collection procedures.

Outcome measures are gathered 30 minutes prior to and following each intervention session to assess immediate effects. A concluding follow-up assessment takes place 1 week after the final session to examine enduring outcomes. Figure 3 illustrates the research design within a single environment. The study protocol (version 1.0 dated March 2, 2026) complies with the SPIRIT (Standard Protocol Items: Recommendations for Interventional Trials) checklist (Table 1).

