**Figure 3. F3:**
[figure not shown]
CONSORT (Consolidated Standards of Reporting Trials) flow diagram. CAA: Chinese art activities; DV: dependent variable; PGP: peer group participation; RC: routine care; VAS: visual analog scale.

**Table 1. T1:** SPIRIT (Standard Protocol Items: Recommendations for Interventional Trials) table with the schedule of enrollment, interventions, and assessments.

	Study period					
	Enrollment (T–1)	Allocation (T0)	Intervention session—Monday (T1)	Intervention session—Wednesday (T2)	Intervention session—Friday (T3)	Intervention session—following Monday (T4)
Enrollment						
Eligibility screening	✓					
Information sheet	✓					
General informed consent	✓					
Group-specific informed consent		✓				
Allocation		✓				
Interventions						
Usual care			✓	✓	✓	
Usual care+CAA^a^			✓	✓	✓	
Usual care+CAA+PGP^b^			✓	✓	✓	
Assessments						
PWB^c^ score	✓					✓
Loneliness score—VAS^d^	✓		✓^e^	✓^e^	✓^e^	✓
Happiness score—VAS			✓^e^	✓^e^	✓^e^	✓
Relaxation score—VAS			✓^e^	✓^e^	✓^e^	✓
Salivary cortisol level			✓^e^	✓^e^	✓^e^	✓

a CAA: Chinese art activities.

b PGP: peer group participation.

c PWB: psychological well-being.

d VAS: visual analog scale.

e This includes pretest and posttest assessment.

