### Outcomes

This research uses a repeated-measure design. In addition to the measurements obtained concurrently with the PWB assessment at baseline and 1 week after the intervention, further pre- and postintervention evaluations are performed for the happiness, relaxation, and loneliness scores and salivary cortisol levels. The schedule of evaluations is outlined in Table 1.

Demographic variables include age, gender, marital status, number of children, educational level, number of chronic diseases, type of residence (private or shared room), length of stay in the older adult center, frequency of monthly visits, and MMSE score.

The PWB score is assessed using the 18-item Chinese version of the PWB scale by Ryff [63]. This scale consists of 18 questions with 3 questions per dimension, covering a total of 6 dimensions: self-acceptance, positive relations with others, autonomy, environmental mastery, purpose in life, and personal growth.

The happiness, relaxation, and loneliness scores are measured using a specific 10-cm visual analog scale (VAS) [64-67]. After a decision is made, the recorded value is measured in millimeters (from left to right) using a ruler to assign a numerical value to the subjective evaluation, with possible scores ranging from 0 to 10. An example of the VAS is shown in Figure 4.

The VAS is a widely recognized and proven effective evaluation tool for subjective experience measurement in the older adult population [64,68-72]. However, studies have also shown that patients with cognitive decline, decreased hand flexibility, and impaired vision may find it difficult to complete, leading to unreliable results [71,73,74]. Therefore, the inclusion criteria stipulated requirements for MMSE scores higher than 24 and the ability to independently read and write. At the same time, the scale uses clearly marked and high-contrast black lines to ensure visual clarity, and during the first use, researchers will explain and demonstrate how to complete the scale to ensure that effective results are obtained from the participants.

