For the testing of objectives 1 and 2, a dual test of intra- and intergroup comparisons will be used. If the data are normally distributed, 2-tailed paired-sample *t* tests will be used for intragroup comparison of the Chinese art activities group or the Chinese art activities and peer group participation group. This will test the intervention effects of the Chinese art activities or Chinese art activities with peer group participation interventions on happiness, relaxation, loneliness, and salivary cortisol levels before and after the intervention (3 times). We will use independent-sample *t* tests to compare the effects of the Chinese art activities or Chinese art activities with peer group participation interventions on happiness, relaxation, loneliness, and salivary cortisol levels with the control group. For the testing of objective 3, an independent-sample *t* test will be used to compare the effects of the Chinese art activities with peer group participation and the Chinese art activities interventions on happiness, relaxation, loneliness, and salivary cortisol levels. For the testing of objective 4, salivary cortisol levels will be the main independent variable, and changes in PWB or relaxation will be divided into 3 quartiles as dependent variables. Ordered logistic regression analysis will be used to explore the association between salivary cortisol and these 2 variables. There will be no additional analyses.

Due to the harmless and short-term nature of this study, there will be very little missing data. Preliminary analysis will be conducted based on the complete case. We will use mean imputation for any missing data within a scale. Following the intention-to-treat principle, participants with intervention data will be included in the analysis.

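### The Wednesday and Friday pretests are post-treatment values, so pre-to-post change at those sessions shows only the immediate increment, and no stated test covers the cumulative or sustained effect

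*Protocol article*

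**What the plan says.** Under Trial Design, "The intervention takes place over 3 sessions in a single week (Monday, Wednesday, and Friday". The text after Figure 2 states the purpose of the session measurements: "Outcome measures are gathered 30 minutes prior to and following each intervention session to assess immediate effects". It gives lasting effects to a separate visit: "A concluding follow-up assessment takes place 1 week after the final session to examine enduring outcomes". Table 1 marks loneliness, happiness, relaxation and cortisol at T1, T2 and T3, and its footnote e reads "This includes pretest and posttest assessment", so each session has its own before and after value.

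Statistical Methods answers objectives 1 and 2 with paired t tests within each active arm on "happiness, relaxation, loneliness, and salivary cortisol levels before and after the intervention (3 times", and with independent-sample t tests against control. Objective 3 uses an independent-sample t test between the two active arms. For the between-arm tests the section names neither the time point nor the value compared (post-session score or change). It then states that nothing further will be analysed beyond the tests listed.

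On an untreated reference, Trial Design says "Baseline evaluations of PWB, loneliness, happiness, relaxation, and salivary cortisol levels are conducted before randomization". At enrollment, Table 1 ticks only PWB and loneliness. The T1 pretest is scheduled for all four session outcomes.

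**The concern.** The T2 and T3 pretests come after one and two active sessions. They are outcomes of treatment as well as starting points for the next session. A change measured from them answers what this session added today. It does not answer how much better off a resident is than without the programme.

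Objectives 1 to 3 ask the second question: whether residents score better after taking part, and better in one active arm than in the other. The Abstract and Trial Design also plan a follow-up for sustained outcomes. If some benefit lasts two days, the T2 and T3 changes leave that part out. Nothing else stated in the article picks it up, because no test is tied to the T1 pretest, to the pre-randomization baseline or to T4.

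**Working it through.** **Inputs.** The planning effect is d = 0.92 (Sample Size), for loneliness, signed here so that positive means benefit. The design has 30 per arm and two-sided α = .05 (sidedness is assumed, since the sample size text does not state it). The share c of a session's post level still present at the next pretest is not in the documents; it is an assumption, shown as a range. Control is taken as stable over the week, and change scores are taken to have the same SD as the planning effect.

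**The plan's own figure.** The article gives at least 25 per group for d = 0.92, power 0.80, α .05. The usual formula gives 2 × (1.960 + 0.842)² / 0.92² = 15.70 / 0.846 = 18.5, so 19, or 20 with the t distribution. The stated 25 is not reproduced, but nothing below depends on it.

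**Step 1: an identity that needs no response model.** For session k,

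post_k − pre_k = (post_k − pre_1) − (pre_k − pre_1).

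The shortfall against the untreated level equals the rise already present in that session's pretest. At session 2 it is 0.92c: 0.23, 0.46 and 0.69 for c = 0.25, 0.5 and 0.75, and zero for c = 0. At session 1 it is always zero.

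**Step 2: what the pattern over sessions looks like.** This depends on how gains build up. Three cases:

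- Saturating: every session ends at 0.92, so the change at sessions 2 and 3 is 0.92(1 − c).
- Diminishing: each session gains half the remaining room below an assumed ceiling of 1.84. At c = 0.5, pre_2 = 0.46, gain (1.84 − 0.46)/2 = 0.69, post_2 = 1.15; pre_3 = 0.575, gain (1.84 − 0.575)/2 = 0.63, post_3 = 1.21.
- Additive: each session adds 0.92 to whatever is there. At c = 0.5, post_2 = 0.46 + 0.92 = 1.38 and post_3 = 0.69 + 0.92 = 1.61.

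| c = 0.5 | Change from own pretest, sessions 1, 2, 3 | Level above T1 pretest, sessions 1, 2, 3 |
|---|---|---|
| Saturating | 0.92, 0.46, 0.46 | 0.92, 0.92, 0.92 |
| Diminishing | 0.92, 0.69, 0.63 | 0.92, 1.15, 1.21 |
| Additive | 0.92, 0.92, 0.92 | 0.92, 1.38, 1.61 |

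At session 2 the own-pretest change recovers 0.46/0.92 = 50%, 0.69/1.15 = 60% and 0.92/1.38 = 67% of the level. In the first two cases the changes shrink while the level holds or rises. In the third the changes are flat and the accumulation cannot be seen.

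**Step 3: power, in the saturating case only.** For a two-sample t test on change scores at session 2 or 3 with 30 per arm (58 df, noncentrality 0.92(1 − c) × √15), power is 0.94, 0.75, 0.42 and 0.14 for c = 0, 0.25, 0.5 and 0.75. With 25 per arm it is 0.89, 0.67, 0.36 and 0.13. Referred to the T1 pretest, the effect stays at 0.92, with power 0.94 at 30 per arm.

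**The case against.** The strongest reply is that the session's own pretest is the right reference for the stated purpose, which is immediate effects. A within-session change does not assume that the previous session has washed out; that assumption enters only if the change is read as total benefit. This stands, and the within-session tests should stay.

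Large carry-over is also not something the article expects. Conceptual Framework defines happiness, relaxation and loneliness as an "immediate, subjective, and transient affective state characterized by momentary feelings", and Limitations warns against expecting long-term results from one week. This stands as a reason to think c may be small. It does not make c zero, and the article plans to measure the same outcomes again at follow-up.

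A reader might infer that the plan will make a working intervention look as if it fades. Carry-over alone does not do that. Diminishing or saturating gains are needed too. They are plausible on a VAS "with possible scores ranging from 0 to 10", but with additive gains the change is 0.92 at every session.

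A reader might also infer that objective 3 could be reversed, with the peer arm looking worse because its benefit lasts longer. That needs three things together: change scores in the between-arm test, saturating gains, and longer persistence in that arm. The article states none of them. A comparison of post-session values would have no contaminated reference, and the objectives' wording fits that reading. What remains is that the article does not say which value is compared.

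Finally, a separate analysis plan might settle this. But the article lists its tests and then closes the list, so as written the gap is fixed rather than deferred.

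**Conclusion.** The point holds in a limited form. The T2 and T3 pretests are post-treatment values. Change from them estimates each session's immediate increment and, if any benefit persists, understates benefit above the untreated level. No stated test is tied to an untreated reference or to T4, so the cumulative and sustained effects that the trial seeks are not tested.

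The size is unknown. The shortfall at session 2 is 0.92c SD, and c is an assumption. The fall in power from 0.94 to 0.42 at c = 0.5 illustrates one case (saturating gains, a change-score test, equal SD, no dropout) and is not an established loss. Session 1 is clean under any assumption, and so are between-arm tests on post-session values if those are what is meant. The documents do not support saying that the intervention will appear to fade, that objective 3 will reverse, or that within-session change is invalid.

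**What to change.** In Statistical Methods:

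- Keep within-session change at T1, T2 and T3, labelled as the analysis of the immediate effect of a session.
- For the programme effect (objectives 1 to 3), compare arms on the post-session values at T1, T2 and T3 and on T4, adjusted for the T1 pretest, or for the pre-randomization baseline where it was collected.
- Treat the T2 and T3 pretests as outcomes (benefit still present about two days after a session), never as untreated baselines.
- Reword the sentence that rules out further analyses so that it allows these comparisons.

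Two details need stating. The T1 pretest is untreated but follows allocation and group-specific consent, so participants may already know their group. T4 is described as one week after a Friday session, yet Table 1 labels it the following Monday; the timing must be reconciled.

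The cost is wording and a few more comparisons to report. Every value needed from T1 to T4 is already in the schedule. Collection ended on October 31, 2025, and analysis was expected to finish in April 2026, so the change should be dated and, if still possible, made before results by group are seen.

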### Participant Allocation

The allocation sequence is produced dynamically by an independent statistician throughout the recruiting phase. Each research site serves as a randomization unit. Using the Minimization Random Program software (version 2.01) [54,55], 30 eligible participants are randomly divided into 2 experimental groups and 1 control group in a 1:1:1 ratio, with 10 participants in each group. The confounding variables are age and number of visits per month. A study found that happiness increases with age before the age of 75 years, but for those over 75 years, the probability of happiness begins to decrease. Therefore, participants will be categorized into age groups of 60 to 75 years and over 75 years [56]. The other confounding variable is the number of visits per month. Older people living in institutions tend to meet with family and friends more frequently, often having more positive and less negative feelings [57]. Hence, participants were classified as having visits 1 to 2 times per month or 3 or more times per month. The categories of confounding variables are shown in Table 2.

The researchers will recruit 30 participants from each institution, resulting in a total of 90 older adults (aged 60‐85 years; individuals with ≤1 year of residence) referred by health care providers. In each institution, the 30 participants are allocated into 3 groups—A, B, and C—comprising 10 participants each. Group A is administered Chinese art activities, group B is administered Chinese art activities and peer group participation, and group C receives routine care.

**Table 2. T2:** Categories of confounding variables in the minimized randomization program.

Confounding variable	Category 1	Category 2
Age (y)	60-75	>75
Monthly visit frequency	1-2 times	≥3 times

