#### Chinese Art Activities Combined With Peer Group Participation

The Chinese art activities with peer group participation intervention, supported by previous studies [51,61], consists of an 80-minute integrated session led by a single researcher (RA). On the basis of established recommendations that at least 4 participants are necessary for effective group interventions [62], the 10 participants in this arm are randomly divided into 2 groups of 5, each facilitated by 1 trained peer volunteer, resulting in 6 individuals per group including the peer volunteer.

Peer volunteers are recruited through self- and staff recommendation. The inclusion criteria are being aged over 60 years, having lived in the center for more than 6 months, having normal cognition, moving freely, having good communication skills, and being enthusiastic to participate. They are responsible for organizing and guiding participants to actively express themselves and encourage each other during the peer group participation phase. One week before the intervention begins, training on research objectives and intervention procedures is conducted through meetings. The training also includes researchers demonstrating communication skills such as organizing peer evaluations, encouraging expression, and strengthening practical abilities through simulated exercises and on-site guidance. The training simultaneously evaluates the competence of volunteers, screening qualified candidates to participate in subsequent interventions. This study will not provide financial compensation to peer volunteers. As an alternative, the research team will give them flowers.

The intervention begins with Chinese art activities that follow the established procedures. After the Chinese art activities are completed, peer group participation is immediately carried out. Peer volunteers organize members to showcase their works. They invite each member to elaborate on the significance of their work while promoting mutual appreciation among group members. Subsequently, participants are encouraged to exchange their works as gifts accompanied by handshakes, smiles, or nods. Finally, peer volunteers conclude the program by sharing personal stories highlighting adaptation to life at the older adult center. Textbox 2 contains information pertaining to the Chinese art activities and peer group participation interventional procedures.

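### The between-arm analysis is limited to unadjusted t tests, which use neither the randomisation factors, nor the repeated measures, nor the peer groups in arm B; the net error is modest and its direction for arm B is unknown

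*Protocol article*

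**What the plan says.** Statistical Methods fixes the comparison of each active arm with control: "We will use independent-sample *t* tests to compare the effects of the Chinese art activities", or of the combined intervention, for happiness, relaxation, loneliness and salivary cortisol. For the two active arms: "For the testing of objective 3, an independent-sample *t* test will be used". After the regression for objective 4 the section ends its list with "There will be no additional analyses". No covariate, centre term, repeated-measures model or peer-group term appears.

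The design described elsewhere has more structure:

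- **Repeated measures.** Outcomes: "This research uses a repeated-measure design". Trial Design and Table 1 give pre and post values at three sessions and a later follow-up (T4).
- **Centre.** Each of three centres contributes 30 participants, randomised 10 per arm within the centre (Participant Allocation).
- **Minimisation.** "The confounding variables are age and number of visits per month", each in two categories (Table 2).
- **Peer groups.** In arm B, "the 10 participants in this arm are randomly divided into 2 groups of 5" at each centre, each with its own peer volunteer, so six groups in all. Arm A participants work at individual desks and can hardly communicate.

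**The concern.** An analysis should reflect how people were allocated and treated. Factors balanced by design shrink the true variance of an arm difference, but an unadjusted t test still counts their variance as noise, so its standard error is too large. Shared group and volunteer effects do the opposite: they raise the true variance in arm B while the t test treats 30 people as independent. Objective 3, arm B against arm A, carries both errors. A baseline covariate would also buy precision in a trial of 30 per arm, and separate t tests make no joint use of three sessions and a follow-up.

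This cannot be left to an unseen analysis plan, because the article names the tests and rules out others.

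**Working it through.** **Inputs.** From the protocol: 30 per arm, 10 per arm per centre, six arm B groups of five. The protocol gives no ICC, no baseline correlation and no share of variance explained by centre, age group and visits. Assumed ranges: ICC 0.05-0.20; share R² 10-30%; correlation rho 0.3-0.7.

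**The plan's own figure.** The nearest one is 25 per group for d = 0.92, power 0.80 and alpha 0.05. Two-sided, 2 × (1.96 + 0.84)² / 0.92² = 18.5, so 19 (20 with the t distribution); 25 is not reproduced. That does not decide this point: 30 per arm has power of about 0.94 at d = 0.92, or 0.85 to 0.92 with arm B clustering at ICC 0.20 to 0.05.

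**Type I error.** Set total variance to 1 and express the ICC as a share of it.

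- The t test takes the variance of the arm difference as 2/30.
- The true variance is (1 − R² + 4·ICC)/30 for arm B plus (1 − R²)/30 for the other arm.
- The ratio of true to assumed variance is v = 1 − R² + 2·ICC.
- Type I error is 2 × [1 − Φ(1.96/√v)].

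Example: R² = 0.10 and ICC = 0.20 give v = 0.90 + 0.40 = 1.30, 1.96/1.140 = 1.72, and an error of 0.086.

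| R² | No clustering (A vs C) | ICC 0.05 | ICC 0.10 | ICC 0.20 | Simulated, ICC 0.05-0.20 |
|---|---|---|---|---|---|
| 0 | 0.050 | 0.062 | 0.074 | 0.098 | 0.061-0.098 |
| 10% | 0.039 | 0.050 | 0.062 | 0.086 | 0.051-0.084 |
| 20% | 0.028 | 0.039 | 0.050 | 0.074 | 0.040-0.072 |
| 30% | 0.019 | 0.028 | 0.039 | 0.062 | 0.033-0.056 |

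Without clustering, simulation gives 0.042 to 0.024 for R² of 10-30%. The formula assumes exact balance and is slightly more extreme; simulated values shift a little with how the factor effects are generated. With centre variance of only 5% or 10%, simulation gives 0.045 or 0.044.

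The two errors cancel when R² = 2·ICC, for example 10% with 0.05 or 20% with 0.10. That would be luck, not design.

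**Adjusting only half.** ANCOVA with baseline and centre but no peer-group term has simulated type I error of 0.063, 0.088 and 0.109 at ICC 0.05, 0.10 and 0.20 (rho 0.5, centre variance 5%). Removing the conservative error exposes the liberal one.

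**Baseline.** Variance relative to a post-score t test:

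| rho | Post score | Change score, 2(1 − rho) | ANCOVA, 1 − rho² |
|---|---|---|---|
| 0.3 | 1 | 1.40 | 0.91 |
| 0.5 | 1 | 1.00 | 0.75 |
| 0.7 | 1 | 0.60 | 0.51 |

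ANCOVA is never worse, since 2(1 − rho) − (1 − rho²) = (1 − rho)² ≥ 0. At rho 0.7 it saves 49% against post scores but only 15% against change scores (0.51/0.60 = 0.85). With rho 0.5, centre variance 5% and no peer-group effect, adjusting for baseline and centre raises power at d = 0.50 from 0.49 to 0.61.

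**The case against.** **The t test is not invalid.** With randomised arms the difference in means is unbiased, power at the planned effect is high, and the trial calls itself exploratory. This stands. The loss is in precision at smaller effects and in the accuracy of the intervals.

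**Arm B comparisons are not shown to be too liberal.** A reader might take 0.098 as the error rate for objective 3. That needs an ICC of 0.20 and factors that explain nothing, which contradicts the argument for adjusting for them. Peer interaction fills only 30 of 80 minutes over three sessions, groups are formed at random, and Limitations says that a short intervention does little to build peer relationships. At ICC 0.01 the error is about 0.052. This stands: the direction is unknown.

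**The baseline may already be used.** A reader might infer that the t tests ignore it. The text compares effects just after describing before-and-after measurements, so change scores are a natural reading. It does not settle the matter. Nor does it say that the between-arm tests are repeated at each session; the mention of three occasions belongs to the paired tests.

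**Wording on centres and visits.** "Each center is treated as a randomization unit" might suggest cluster randomisation, but Participant Allocation shows individuals allocated within each centre. Also, "participants were classified as having visits 1 to 2 times per month or 3 or more times per month" leaves no cell for residents with no visits. Recruitment has ended, so neither can change the allocation; they are side points.

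**Conclusion.** The concern holds in a limited form. The plan commits to unadjusted t tests, and to nothing further, for a design that is stratified by centre, minimised, repeated over time and partly clustered.

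- **A versus C:** affected only by the omitted factors, hence conservative; type I error about 0.042 to 0.024 at R² of 10-30%, closer to 0.045 if centre alone matters and explains 5%.
- **B versus A and B versus C:** two opposing errors; net type I error between about 0.03 and 0.09, direction unknown.
- **Precision:** ANCOVA is at least as precise as either version of the t test; the gain depends on rho and on which score was meant.

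Every magnitude rests on assumed inputs. The documents do not support a claim that the trial would produce false positives, or that the baseline is certainly discarded. In a declared exploratory trial this is something that should be fixed, not a fatal flaw.

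**What to change.** Before allocation is revealed to the analysts, record a dated change that:

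1. Replaces the between-arm t tests with one linear mixed model per outcome over the three post-session values and T4. Fixed effects: arm, time, arm by time, baseline, centre, age group, and visit group as recorded in the minimisation. Add a participant random effect. Report A versus C, B versus C and B versus A from it.
2. Uses ANCOVA for PWB at T4 with the same covariates. Objectives 1 to 3 include PWB, but Statistical Methods names no between-arm test for it.
3. Settles the baseline. Trial Design says all five outcomes were measured before randomisation; Table 1 ticks only PWB and loneliness at enrolment. Reconcile the two. Use the pre-randomisation value where it exists, otherwise the session 1 pre-session value. The latter is taken after participants have signed group-specific consent, so it is second best for self-rated outcomes.
4. Adds, for comparisons involving arm B, a peer-group random intercept in arm B only, with small-sample degrees of freedom (Satterthwaite or Kenward-Roger), at least as a sensitivity analysis. Covariates alone do not protect these comparisons.

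While there, describe centre as a stratum and state how any resident without visits was coded.

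**Cost.** Revised wording and standard software. Centre, age and visit frequency are already recorded; the baseline for happiness, relaxation and cortisol depends on step 3. Six groups estimate the peer-group variance poorly, so intervals involving arm B may widen.
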